## Abstract

**Background:**

Major depressive disorder (MDD) is a world-leading cause of disability. The available treatments are not effective in all patients, and there is a significant need for more effective treatment options. Here we present the protocol for an investigator-initiated and publicly funded trial of MDMA-assisted therapy (MDMA-AT) for MDD. This single-site, open-label study investigates the proof of principle and safety of MDMA-AT in participants with MDD and provides an initial impression of treatment effectiveness.

**Methods:**

A total of 12 participants [>18 years] with DSM-5 diagnosis of MDD will receive a flexible dose of MDMA in a therapeutic setting on two dosing days over a 4 week period preceded by three preparatory sessions. Each MDMA dosing session will be followed by three integration sessions. The primary outcome is change in MDD symptom severity, as measured by the mean change in MADRS scores from Baseline to 8 weeks after the second MDMA session. The secondary outcome is change in functional impairment, as evaluated by the mean change in Sheehan Disability Scale scores from Baseline to 8 weeks after the second MDMA session. Safety measures include vital signs, the incidence of Adverse Events and suicidality as measured by the Colombia-Suicide Severity Rating Scale.

**Discussion:**

This proof of principle trial will inform the development of fully powered clinical trials, optimize the protocol for the administration of MDMA-AT in participants with MDD and explore uncertainties including barriers to recruitment, retention and acceptability of MDMA-AT as a treatment for MDD.

**Clinical trial identification:**

EudraCT number 2021-000805-26.

## Background and rationale

Major depressive disorder (MDD) is a world-leading cause of disability, affecting more than 300 million people (1). Current treatment of MDD, including pharmacotherapy and psychotherapy are well-established and widely used (2, 3). However, the effect sizes are only small to moderate, the available treatment options are not beneficial for all MDD patients (3, 4), as many as 30% are regarded as treatment resistant (5), and antidepressant medications can have substantial adverse effects (3, 5). While the psychopharmacological revolution delivered a series of new drugs from 1950 to 1980's, few if any new agents have been developed during the last two decades (6, 7). The hope that advances in the neurosciences would enable highly effective forms of rational drug design have been disappointing (8). The primary treatments for MDD are psychotherapy and antidepressant medications (9) and large meta-analyses have concluded that the effect of these treatments to be comparable (10). The combination of pharmacotherapy and psychotherapy has shown to be the most effective treatment (11).

Decades after the restrictions of clinical research due to the international scheduling of 3,4-methylenedioxymethamphetamine (MDMA) and classical psychedelic drugs, there is now optimism associated with the treatment of mental disorders with these compounds in conjunction with psychotherapy. Randomized, controlled trials have demonstrated preliminary evidence for an antidepressant effect of the classical psychedelic psilocybin in participants with a life-threatening disease (12–14). A randomized, waiting list-controlled study found rapid and sustained antidepressant effect from psilocybin with a large effect size in participants with MDD (15). A randomized, double-blind study found psilocybin and escitalopram to be equally effective for MDD when analyzing the primary outcome measure. However, secondary outcome measures generally favored psilocybin (16). If MDMA and classical psychedelic drugs prove to be safe and effective in clinical trials, it will represent a new principle in the treatment of mental disorders and addiction: the facilitation of the psychotherapeutic process with an enduring effect and a rapid onset from one or a few doses as compared to the daily administration of currently available antidepressants.

MDMA acts primarily as a monoamine release and reuptake inhibitor, with a different mechanism of action than conventional antidepressant drugs. MDMA enhances synaptic levels of serotonin, and to a smaller extent norepinephrine and dopamine (17–20). Furthermore, MDMA affects neuroplasticity and increases the levels of oxytocin, vasopressin, cortisol and prolactin (21). Oxytocin is associated with prosocial behavior and increased trust and strengthening of the therapeutic alliance (22), supporting the use of MDMA in combination with therapy (23). Many MDD patients have excess activity of the hypothalamic-pituitary-adrenal cortex (HPA) axis, potentially causing neurobiological changes including hippocampal atrophy (24). The indirect effects of MDMA on neurohormone release may help regulate the HPA axis, which is a central psychopathological feature of MDD (25).

MDMA-assisted therapy (MDMA-AT) is a novel alternative approach for treatment of mental disorders (26). In this treatment model, MDMA is regarded as a catalyst for the psychotherapeutic process (27), and is administered with therapy in 2 or 3 monthly 8-h sessions, preceded by preparatory and followed by integrative therapy sessions (28). Six phase 2 trials and one phase 3 trial have demonstrated significant effects of MDMA-AT for post-traumatic stress disorder (PTSD) compared with placebo, with large effect sizes (29, 30). In 2017, the Food and Drug Administration (FDA) designated MDMA-assisted psychotherapy of PTSD a “breakthrough therapy” (26). MDMA-AT has shown preliminary positive effects in other indications as well (31–33), however it has not been investigated in the treatment of MDD until now.

In the following text, we will provide the rationale for an MDMA-AT trial for MDD. Our design is based on the first study of psilocybin for treatment-resistant depression, which was an open label trial in a sample of 12 participants (34), and a MDMA-AT trial for PTSD, for which the study team was a site (35).

Case reports from the 1970's and 1980's described therapeutic benefits in a variety of psychological disorders, including depression, although no clinical trials were conducted at that time before MDMA was scheduled as an illegal drug (36). Greer and Tolbert summarized the potential benefits in 29 patients that received MDMA as an adjunct to psychotherapy (27). Nine subjects with a psychiatric diagnosis reported significant relief, and all four patients with a depressive disorder reported improvement (27).

MDMA-AT has shown preliminary but promising results in other indications, namely in the treatment of social anxiety in autistic adults (31), anxiety associated with a life threatening illness (32) and alcohol use disorder (33). Although these results need to be confirmed in larger, randomized trials, they indicate transdiagnostic benefits from MDMA-AT, which in turn could be extended to MDD.

Significant and immediate antidepressant effects of MDMA-AT have been demonstrated in two published phase 2 PTSD trials (37, 38). In the pooled analysis of all six phase 2 trials, there was a trend toward significance, whereas the phase 3 trial showed also an antidepressant effect (28, 30). A significant proportion of MDD patients have experienced traumatic events earlier in life, and childhood trauma is associated with depression in adulthood (39). To the extent that unprocessed traumatic events is a causative factor in some patients with depression, this would suggest that the benefit from MDMA-AT observed in the PTSD trials may also apply to MDD trials (40).

MDD often relapses after initial response or remission (41). The PTSD studies show not only a lasting, but also increased positive effect on PTSD symptoms at the long-term follow-up one year after MDMA-AT (28, 29). If the results from the PTSD trials are applicable to MDD, sustained efficacy after a few doses might prevent relapse and could also be beneficial in comparison to the daily administration of current available medication and the associated adverse effects.

Although speculative, indirect evidence from PTSD studies makes it possible to hypothesize a similar impact on MDD, including improved self-knowledge, sleep regulation, mentalization skills, coping strategies, emotion regulation, and cognitive insights (28). As MDMA temporarily increases interpersonal trust, while also reducing avoidance and psychological defenses, it might be helpful in the processing of memories and emotions in MDD same as in PTSD (42). Furthermore, MDMA-AT allows for an experience of safety, trust and collaboration with the therapists (43). Overall, MDMA-AT holds promise as a catalyst to the therapeutic process and enhancer of the therapeutic alliance.

Although recreational use of MDMA sometimes is associated with low mood in the days following ingestion, this is less of a concern when MDMA is administered clinically (44). There are several reports on adverse events from recreational use of MDMA, however these findings are based on studies with sub-optimal methodology (45). This includes the inclusion of polydrug users, the use of higher doses than in a clinical setting and that the drugs taken contain other substances in addition to or instead of MDMA. Pure MDMA has been well-tolerated in controlled studies in humans (46). Close to 200 participants have received MDMA-AT for PTSD in phase 2 and 3 trials (28). The US FDA has declared MDMA to have a satisfactory safety profile for clinical trials to be conducted (26). Nevertheless, clinical trials with MDMA must be careful to address potential adverse effects and risk of long-term harmful effects.

The primary objective of this pilot study is to explore the proof of principle and safety of open-label MDMA-AT with a flexible dose of MDMA in participants with MDD, and provide an initial assessment of treatment effectiveness. This proof of principle study will inform the development of fully powered RCTs, optimize the protocol for the administration of MDMA-AT in participants with MDD and explore uncertainties including barriers to recruitment, retention and acceptability.

## Methods and analysis

### Design

This single-site, open-label study investigates the proof of principle and safety of MDMA-AT in 12 participants diagnosed with MDD and provides an initial assessment of potential treatment effectiveness.

A study protocol of MDMA-AT for PTSD (35), from which the study team has experience as a study site, informed the development of the present study protocol. In the treatment period, MDMA is given on two dosing days ~1 month apart. A supplemental half-dose of MDMA will be provided to extend the effects unless tolerability issues. A total of nine 90-min non-drug preparatory and integrative psychotherapy sessions will precede and follow the MDMA dosing sessions. Dosing sessions are followed by an overnight stay.

As in (35), for each participant, the study will consist of:

° Screening period: phone screen, informed consent, eligibility assessment, and enrollment of eligible participants.° Preparatory period with enrollment confirmation: medication tapering, preparatory sessions and baseline assessments.° Treatment period: two monthly dosing sessions and associated integrative sessions over ~8 weeks. The aims of the integration sessions are to continue the exploration of emotions and memories and to apply any new insights and experiences into daily life.° Follow-up period and study termination: 4 weeks with no study visits, followed by outcome measures and study termination visit.

### Recruitment and participant population

We will recruit adult men and women, 18 years of age and older, with at least moderate depression at time of enrollment. Participants with depression are defined as those who meet the Diagnostic and Statistical Manual of Mental Disorders, 5th Edition (DSM-5) (47) diagnostic criteria for single or recurrent episode of MDD without psychotic features, with a duration of more than 12 weeks and < 2 years at time of enrollment. Participants will be recruited through referrals from general practitioners, psychiatrists, and psychotherapists. During screening, the participant may be asked to taper concomitant medications, if needed. The key inclusion and exclusion criteria are shown in Table 1. Key inclusion and exclusion criteria.

**Table 1 T1:** Key inclusion and exclusion criteria.

**Inclusion criteria [informed by (35)]**
• At Screening, meet DSM-5 criteria for current MDD with a symptom duration of more than 12 weeks and less than 2 years • At Baseline, have at least moderate MDD per MADRS and symptoms in the last month constituting a MADRS Total Severity Score of 20 or greater • ≧18 years of age • Sufficient competency in the Norwegian language • Capacity to provide consent • Agreement to provide a support person who is willing and able to be reached by the investigators in the event of a participant becoming suicidal or unreachable • Agreement to follow specific lifestyle modifications **Exclusion criteria**
• Electroconvulsive Therapy (ECT) or ketamine within 12 weeks of enrollment • Current or previously diagnosed psychotic disorder, significant history of mania, or evidence of a personality disorder • Current eating disorder with active purging • Current moderate or severe alcohol or cannabis use disorder within the 12 months prior to enrollment • Active illicit (other than cannabis) or prescription drug substance use disorder at any severity within 12 months prior to enrollment • Current serious suicide risk, as determined through psychiatric interview, responses to C-SSRS, and clinical judgment of the investigator will be excluded; however, history of suicide attempts is not an exclusion • The use of any psychoactive medication not approved by the research team from Baseline through Study Termination (with the exception of gabapentin or certain opiates for pain control) • Positive pregnancy test or breastfeeding. Unable to agree to the use of highly effective contraception methods • History of any medical condition that could make receiving a sympathomimetic drug harmful because of increases in blood pressure and heart rate. This includes, but is not limited to, a history of myocardial infarction, cerebrovascular accident, or aneurysm. Mild, stable chronic medical problems (diabetes mellitus type 2, for example) are allowed in the study if the symptoms from that disease are not being confused with side effects from MDMA or interfering with study participation • Uncontrolled hypertension. Participants with well-controlled hypertension might be enrolled if acceptable cardiovascular risk (family history, smoking, lipid levels, body weight, level of physical activity) and no signs of ongoing cardiovascular or cerebrovascular disease from history, physical exam or ECG supplemented by echocardiography or nuclear imaging, and carotid ultrasound • History of ventricular arrhythmia at any time, other than occasional premature ventricular contractions (PVCs) in the absence of ischemic heart disease • Have a marked Baseline prolongation of QT/QTc interval e.g., repeated demonstration of a QTc interval >450 milliseconds [ms] in males and >460 ms in females (corrected by Fridericia's formula) • Have a history of additional risk factors for Torsade de pointes (e.g., heart failure, hypokalemia, family history of Long QT Syndrome) • Symptomatic liver disease or significant liver enzyme elevation • History of clinically significant hyponatremia or hyperthermia • Weight < 48 kilograms (kg)

As this is a feasibility study, we are interested in obtaining a preliminary impression of how MDD patients can be recruited to an MDMA-AT study, and to what extent the patient remains in the study as a proxy for the acceptability of the treatment. We will report the number of potential participants that were phone screened, as well as the number of participants that were considered as screen failures (not eligible after signed informed consent form and therefore not enrolled in the study), pre-dosing early terminations (initially enrolled, but deemed ineligible before the first MDMA session), post-dosing early terminations (Participants who choose to stop treatment, but who attend study visits and participate in outcome assessments), dropout (Participants who withdraw their consent and do not want to contribute to further study visits or measurements), and lost to follow-up (Participants who do not show up for study visits and who are unable to be contacted by the site staff).

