### Study visits

The Study Structure Overview is shown in Figure 1. Full screening may take 2 to 5 weeks after phone screening. Enrollment takes place at the completion of Screening. Safety information and measures will be collected up to 1 month after the participant's last therapy session during the Follow-Up Period. We will recruit actively up to enrollment of 12 participants. The Preparatory Period begins at enrollment and can be as short as 2 weeks. If the participant uses psychotropic medication, the preparation period can be up to 8 weeks to ensure adequate tapering until discontinuation plus one week of stabilization without medication.

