**Figure 1 F1:**
[figure not shown]
Study structure overview.

The preparatory period ends at enrollment confirmation and thus the start of the treatment period. The treatment period lasts approximately 8 weeks and includes two dosing sessions 3-5 weeks apart and three non-drug integrative sessions after each of the two. After the final Integrative Session 2.3 (Visit 12), participants will enter the follow-up period with no study visits for ~4weeks, followed by the Primary Outcome MADRS T2 (Visit 13). The study procedures are presented in Table 2.

**Table 2 T2:** Time and events – study procedures [informed by (35)].

**Time and events – study procedures**	**Screening period (2 to 6 weeks)**			**Preparatory period w/enrollment confirmation** **(2 to 11 weeks)**			
	**Screening**		**Enrollment**	**Preparatory**		**Baseline MADRS T1**	**Baseline & enrollment confirmation**
**Visit**	**Phone screening**	**Screening**	**V0**	**V1**	**V2**	**V3**	**V4**
**Visit description**	**Phone calls**	**In-person visits & labs**	**Enrollment**	**Prep 1**	**Prep 2**	**MADRS T1 assessment at site**	**Prep 3 & enrollment confirmation**
Initial phone screen	✓						
Informed consent	Send Copy	✓					
Follow-up phone screen	✓						
Assess eligibility	✓	✓	✓	✓	✓		✓
Medical/psychiatric history	✓^A^	✓		✓	✓		✓
Past/current medication & adherence	✓	✓		✓	✓		✓
Weight, resting vitals		✓					
Physical exam		✓					
ECG & rhythm strip^H^		✓					
Clinical lab tests		✓					
Drug screen		✓					✓
Pregnancy screen		✓					✓
Enter participant in eCRF		✓					
Record				✓	✓	✓	✓
Medication taper			✓	✓	✓		
Study enrollment			✓				✓ Confirmed
All AEs^B^			✓	✓	✓		✓
90-min preparatory session				✓	✓		✓
Phone call follow-up^C^					✓		
**Time and events – study procedures (continued)**	**Treatment period** ~**8 weeks (**+**/-3 weeks)**								**Follow-up period & study termination (**~**4 weeks)** **13 weeks (**+**/-3 weeks) post baseline**	
	**Treatment 1**				**Treatment 2**				**Outcome**	**Study Termination**
**Visit**	**V5**	**V6**	**V7**	**V8**	**V9**	**V10**	**V11**	**V12**	**V13**	**V14**
**Visit description**	**Exp. 1**	**Int 1.1**	**Int. 1.2**	**Int 1.3**	**Exp. 2**	**Int. 2.1**	**Int 2.2**	**Int 2.3**	**MADRS T2 assessment at site**	**Study termination**
Past/current medication and adherence	✓	✓	✓	✓	✓	✓	✓	✓		✓
Drug screen	✓				✓					
Pregnancy screen	✓				✓					
Record	✓	✓	✓	✓	✓	✓	✓	✓	✓	
All AEs^D^	✓	✓	✓	✓	✓	✓	✓	✓		✓
Administer IP	✓				✓					
8-hour Exp. Session	✓				✓					

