BP, Pulse, Temperature^E^	✓				✓					✓^F^
Overnight Stay	✓				✓					
90-min Integrative Session		✓	✓	✓		✓	✓	✓		
Phone Call Follow-up^G^		✓				✓				
Weight										✓

^A^At Screening, collect data on previous hospitalizations, healthcare utilization and economic productivity. Request participants to obtain medical/psychiatric records to bring to the in-person screening.

^B^All Adverse Events (AEs) includes collecting Serious Adverse Events, AEs of Special Interest, AEs of Psychiatric Status, AEs requiring medical advice or attention, AEs that indicate withdrawal of a participant, and all other AEs.

^C^If needed, call participant to confirm medication tapering and stabilization is complete prior to Visit 3.

^D^All Adverse Events (AEs) includes collecting Serious Adverse Events, AEs of Special Interest, AEs of Psychiatric Status, AEs requiring medical advice or attention, AEs that indicate withdrawal of a participant, and all other AEs.

^E^During Dosing Sessions, vitals are measured before Investigational Product administration, immediately before the supplemental dose is administered (or would be, if supplemental dose not given), and approximately 8 h after initial dose, and as needed.

^F^At Study Termination, only blood pressure needs to be measured.

^G^4 days of phone call follow-up: Day 2 and 7 after the Dosing Session, with two additional calls in between.

^H^We do not repeat the ECGT during the MDMA dosing sessions, since we will avoid possible interference with the therapy facilitated by MDMA.

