### Outcome measures

#### Primary outcome measure

The primary outcome measure will capture the change in MDD symptom severity, as measured by the mean change in MADRS scores from Visit 3 (Baseline) to Visit 13 (approximately 12 weeks post Baseline) (49).

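### The Visit 3 MADRS appears to be both the entry criterion (20 or more) and the baseline of the primary change score, so regression to the mean favours improvement in this single-arm trial

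*Protocol article*

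**What the plan says.** All references are to the protocol article.

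- **Severity criterion.** Table 1 says: "At Baseline, have at least moderate MDD per MADRS", defined by "symptoms in the last month constituting a MADRS Total Severity Score of 20 or greater".
- **Primary outcome.** It is the "mean change in MADRS scores from Visit 3 (Baseline) to Visit 13", so Baseline means Visit 3.
- **Order of visits.** Table 2 places MADRS T1 at V3, and eligibility review with enrollment confirmation at V4. It lists no other MADRS before treatment. The text under Figure 1 adds: "The preparatory period ends at enrollment confirmation and thus the start of the treatment period".
- **Recruitment text.** The section on recruitment and participant population describes adults "with at least moderate depression at time of enrollment". Table 2 puts enrollment at V0, before the preparatory sessions, and heads V4 (not V3 alone) as a baseline visit.
- **Taper.** For users of psychotropic medication, the section on study visits allows time for "adequate tapering until discontinuation plus one week of stabilization without medication". Footnote C of Table 2 provides, where needed, for staff to "call participant to confirm medication tapering and stabilization is complete prior to Visit 3".
- **Design.** There is one open-label group of 12 and no comparator.

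**The concern.** A score that must reach 20 for a participant to stay in the study is, on average, a little too high among those who stay. Some candidates pass because they were rated on a bad day or by a generous rating, and their next score tends to be lower whatever is done in between. If the same score is the starting point of the change, that fall counts towards the primary result. In a randomised trial it would cancel between arms; here nothing cancels it.

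The one-month look-back raises a second, separate question. For someone who has just stopped an antidepressant, it is unclear which state the baseline describes.

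The article says the trial will inform fully powered trials. A change score that is too large in a known direction could carry over into their planning.

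**Working it through.** **Is it the same score?** Table 1 applies the cut-off at Baseline. The primary outcome defines Baseline as Visit 3. Table 2 shows the MADRS at V3, confirms enrollment at V4 and shows no earlier MADRS. Taken together, the selecting score is the V3 score. This is an inference: Table 2 also omits the C-SSRS, SDS and BDI-II, so it is not a full schedule of assessments.

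**Size of the regression effect.** The article gives no SD, correlation, effect size or power, so there is no figure of its own to reproduce. Inputs:

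- cut-off 20 (Table 1);
- mean mu and SD of candidates reaching V3 (assumed);
- correlation r between V3 and V13 with no treatment effect (assumed).

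For a normal score selected at 20 or more, with z = (20 − mu)/SD, the expected fall without any treatment effect is

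(1 − r) × SD × φ(z) / (1 − Φ(z)).

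With SD = 6:

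| mu | r | φ(z)/(1 − Φ(z)) | Calculation | Expected fall |
|---|---|---|---|---|
| 20 | 0.5 | 0.80 | 0.5 × 6 × 0.80 | 2.39 |
| 22 | 0.6 | 0.60 | 0.4 × 6 × 0.60 | 1.44 |
| 25 | 0.5 | 0.35 | 0.5 × 6 × 0.35 | 1.06 |
| 25 | 0.9 | 0.35 | 0.1 × 6 × 0.35 | 0.21 |
| 28 | 0.8 | 0.18 | 0.2 × 6 × 0.18 | 0.22 |

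(Results use unrounded ratios.) Over a wider grid (mu 20 to 30, SD 5 to 8, r 0.5 to 0.9) the range is 0.03 to 3.2 points. Simulation of 1,000,000 candidates in each of four scenarios agreed with the formula.

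**Scale.** With n = 12 and an assumed SD of change of 6 to 10, the 95% confidence half-width is 2.201 × SD/√12, or 3.8 to 6.4 points.

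**Effect of a separate qualifying score.** The simulated fall from V3 to V13 was:

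| mu, SD, r | V3 qualifies | Earlier score qualifies, independent errors | Earlier score qualifies, serially decaying correlation | Both scores must be 20 or more (independent errors) |
|---|---|---|---|---|
| 25, 6, 0.5 | 1.05 | 0.00 | 0.53 | 0.84 |
| 25, 6, 0.7 | 0.64 | 0.00 | 0.45 | 0.46 |
| 22, 8, 0.5 | 2.58 | 0.00 | 1.28 | 1.96 |
| 28, 6, 0.8 | 0.22 | 0.00 | 0.18 | 0.16 |

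Under serial decay the share that remains equals the correlation: r(1 − r) against (1 − r). About half goes at r = 0.5 and less at higher r, where the bias is smaller to begin with.

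**Look-back.** Taking a month as four weeks, and one medication-free week as the only interval promised, 4 − 1 = 3 weeks of the rated period can precede that week. This is the extreme case, and it concerns only participants who tapered, whose number is not given. The article states no recall window for T2.

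**Timing labels.** The recruitment text ties moderate depression to enrollment (V0 in Table 2). Table 1 ties the MADRS cut-off to Baseline. The primary outcome puts Baseline at V3, and Table 2 uses the word again for V4. A reader cannot tell with certainty which visit decides severity.

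**The case against.** The strongest reply is that this is a small open-label pilot. It claims only an initial impression of effectiveness and admits that it cannot settle the question. Beside a half-width of 3.8 to 6.4 points, a bias near one point is hard to see. The larger regression figures also assume that many candidates fail at V3: 50% at a mean of 20 and about 37% at a mean of 22 (SD 6), which is a lot for people already judged at least moderately depressed at enrollment. This stands as a limit on size. It does not remove the bias, which has one direction, and the stated limitation does not mention it.

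The recruitment text and Table 1 can also be read together: moderate depression at V0, then a MADRS criterion confirmed later. The recruitment text gives no cut-off, and the article expressly foresees people who enroll and are then found ineligible before the first MDMA session. So this is unclear labelling, not a flat contradiction. A screening MADRS in the full protocol also cannot be excluded.

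A reader might infer that tapering inflates the V3 score and so also counts as treatment benefit, and might add points for it. The documents do not support that. Withdrawal symptoms or worsening during the taper would raise V3, while weeks still on an effective drug would lower it. Nothing in the article fixes the sign, the size or the number of participants affected.

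**Conclusion.** On the article's wording, the score that admits participants is also the start of the primary change score, and with no control arm this biases the mean change towards improvement. With SD 6, an unselected mean of 20 to 28 and a correlation of 0.5 to 0.8, the bias is about 0.2 to 2.4 MADRS points; at a mean of 25 with correlation 0.5 to 0.9 it is roughly 0.2 to 1.1. All these inputs are assumptions. The bias is modest but systematic, and a confidence interval around the mean change does not include it.

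The look-back is a matter of interpretation: for tapered participants the baseline may describe a mixture of states, with unknown direction of effect, so no points should be added for it. The change is worth making because it is cheap, not because the bias could by itself explain a large observed improvement.

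**What to change.** 1. Take a qualifying MADRS at screening or V0 and apply the severity criterion to it. V3 then serves as an analysis baseline separate from the selecting score. Requiring 20 or more at V3 as well would keep most of the bias (0.84 of 1.05, and 1.96 of 2.58, in the illustration), so the plan should say how a V3 score below 20 is handled.
2. Reconcile the recruitment text, Table 1, the primary outcome and the Table 2 headings on which visit is Baseline and when severity is judged.
3. State one recall window for T1 and T2, short enough that T1 does not reach back into the taper. This makes clear which period is rated; it does not remove effects of recent discontinuation.
4. Report the V0 to V3 change descriptively, noting that it mixes regression to the mean, taper and preparatory sessions and does not isolate taper. Report the V3 to V13 change by taper status.
5. Name regression to the mean as a limitation, since item 1 reduces the bias but removes it fully only if rating errors are independent between visits.

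Cost: one extra MADRS rating and some rewording. Some participants may score below 20 at V3, and the headline change may be slightly smaller.
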